**Methods:**

A total of 120 women presenting with moderate depressive symptoms (17-item Hamilton Depression Rating Scale score 17‐23), aged 18 to 45 years, will be randomized to receive either the 10-week 3D Program or informational video content, with both groups continuing treatment as usual. The 3D Program will integrate personalized therapist support, self-guided digital modules, and a moderated online group, with content cocreated alongside women with lived experience of depressive symptoms. The primary outcome will be the change in depressive symptom severity, measured by the 17-item Hamilton Depression Rating Scale at 12- and 26-week postbaseline assessments. Secondary outcomes will include functioning, quality of life, perceived stress, and menstrual-related distress. Additionally, the study will explore potential biological predictors of treatment response, analyzing metabolic markers related to tryptophan metabolism and adrenal steroid pathways across multiple biological matrices. Data analyses will use linear mixed-effects models and multivariate techniques to examine treatment effects and possible biomarker associations.

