#### Procedure

Assessments will be conducted at 3 time points: baseline (T0), postintervention (12 weeks after baseline, T1), and follow-up (26 weeks after baseline, T2).

The baseline assessment will include the collection of sociodemographic and clinical data, the administration of primary and secondary outcome measures, a gynecological consultation to assess hormonal and menstrual health, and the collection of biological samples.

At T1 and T2, follow-up assessments will include the administration of primary and secondary outcome measures as well as biological sample collection.

All psychological assessments will be carried out by a trained professional (psychologist, physician, psychiatrist, or psychiatric nurse), gynecological examinations will be performed by a licensed gynecologist (MD in obstetrics and gynecology), and biological samples will be collected by a registered nurse. Participant timeline, including the schedule of enrollment, interventions, and assessments, is outlined in Table 1. All professionals with direct participant contact—whether via teleconference or in-person—will be women. This decision was reached by consensus within the focus group of women with a lived experience of depression, who expressed that sensitive topics (eg, hormonal changes, gender discrimination, and sexuality in the context of depression) would be better understood by female professionals and that participants would feel more comfortable accordingly.

**Table 1. T1:** SPIRIT (Standard Protocol Items: Recommendations for Interventional Trials) participant timeline.

Study procedure	Trial period					
	Preintervention			Intervention	Postintervention	Follow-up
Time point	–t0	T0	T0	—^a^	T1	T2
Weeks	0	1	2	3‐12	12	26
Enrollment						
Eligibility screen	*✓*					
Informed consent		✓				
Inclusion		✓				
Randomization		✓				
Interventions						
Intervention (3D Program)				✓		
Control group (informational videos)				✓		
Screening assessments						
Sociodemographic information		✓				
Medical and psychiatric history		✓				
Gynecological visit			✓			
Primary outcome						
HDRS-17^b^		✓			✓	✓
Secondary outcomes						
WHODAS 2.0^c^		✓			✓	✓
EQ-5D-5L^d^		✓			✓	✓
PSS^e^** **		✓			✓	✓
MEDI-Q^f^** **		✓			✓	✓
Biological samples						
Plasma			✓		✓	✓
Saliva			✓		✓	✓
Urine			✓		✓	✓
Nails			✓		✓	✓
Hair			✓		✓	✓

a Not applicable.

b HDRS-17: 17-item Hamilton Depression Rating Scale.

c WHODAS 2.0: World Health Organization Disability Assessment Schedule 2.0 (36-item version).

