#### Primary Outcome Measures

Change in depressive symptoms from baseline (T0) to 12 weeks (T1) and 26 weeks (T2) was assessed using the clinician-administered HDRS-17, which was validated in Spanish [23,24]. The HDRS-17 total score ranges from 0 to 52, with higher scores indicating more severe depression.

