#### Predictors and Covariate Analysis

Additional analyses will identify baseline predictors of clinical improvement using LMMs and multiple linear regression. To address the dynamic nature of psychological factors, perceived stress (PSS) and menstrual distress (MEDI-Q) will be modeled as time-varying covariates within the LMM framework rather than as static baseline moderators. This allows for the assessment of whether longitudinal fluctuations in these variables are associated with concurrent changes in depressive symptoms. Furthermore, exploratory multilevel mediation analyses may be conducted to examine if changes in PSS or MEDI-Q partially mediate the intervention’s effect on HDRS-17 trajectories.

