#### Metabolomics

Partial least squares regression and multiple regression analyses will be used to model associations between metabolite profiles, their changes over time, and changes in depressive symptoms. Variable importance in projection scores and cross-validation techniques will be used to evaluate model performance and identify key predictive biomarkers. Additionally, metabolomic changes will be assessed through exploratory factor analysis, grouping variables into latent factors. It should be noted that the study was originally conceptualized and powered as a confirmatory superiority RCT; therefore, the metabolomics substudy should be considered secondary and may be limited by this design. Nevertheless, given the scarcity of data in this biological field of research, we believe it is worthwhile to conduct this post hoc exploratory proof-of-concept study.

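### The Metabolomics section draws its predictive biomarkers from models that may include metabolite changes measured at the same visits as the HDRS-17 change, so concurrent correlates of recovery can be labelled predictive

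*Protocol article*

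**What the plan says.** The abstract's Methods paragraph says that "the study will explore potential biological predictors of treatment response".

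The Predictors and Covariate Analysis section handles two kinds of question separately. For the first, "Additional analyses will identify baseline predictors of clinical improvement using LMMs and multiple linear regression". For the second, perceived stress (PSS) and menstrual distress (MEDI-Q) enter as time-varying covariates, to assess "whether longitudinal fluctuations in these variables are associated with concurrent changes in depressive symptoms".

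The Metabolomics section does not keep this separation. Its PLS and multiple regression analyses are to "model associations between metabolite profiles, their changes over time, and changes in depressive symptoms". The next sentence says that VIP scores and cross-validation "will be used to evaluate model performance and identify key predictive biomarkers".

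On timing, the Procedure section states: "At T1 and T2, follow-up assessments will include the administration of primary and secondary outcome measures as well as biological sample collection". The Primary Outcome Measures section takes the HDRS-17 change from T0 to T1 (12 weeks) and from T0 to T2 (26 weeks). No lag between metabolite change and symptom change is stated.

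**The concern.** A predictor of response has to be known before the response. A T0-to-T1 metabolite change is observed at the visit where the T1 HDRS-17 is scored. It could be a cause of improvement, a consequence of it, or a marker of current mood, and it cannot be used to decide who should receive the program.

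If such changes are among the candidate variables, two outputs lose their stated meaning:

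- **VIP ranking.** VIP rewards covariance with the outcome, so a metabolite that only tracks mood can rank highly.
- **Cross-validated performance.** Cross-validation guards against overfitting. It does not guard against an explanatory variable measured together with the outcome, because the held-out woman's metabolite change comes from her outcome visit too.

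At stake is what the biomarker substudy can conclude. The abstract's Conclusions paragraph hopes that the findings will prepare later trials of response predictors. Correlates of recovery passed on as predictors would misdirect those trials.

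**Working it through.** **1. The plan's own figure.** The Sample Size Calculation section gives f = 0.15, two groups (k), three measurements (m), correlation ρ = 0.5, ε = 1, α = .05 and power 0.90. For the within-between interaction:

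- λ = f²·N·m/(1 − ρ) = 0.0225 × 96 × 3 / 0.5 = 12.96
- df1 = (k − 1)(m − 1) = 2; df2 = (N − k)(m − 1) = 94 × 2 = 188
- power = 0.902 at N = 96, and 96 / 0.80 = 120

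The stated 96 and 120 reproduce. The point does not rest on them; 96 serves below only as a plausible number of completers.

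**2. The sections side by side.**

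| Section | Explanatory variable | Outcome | Label |
|---|---|---|---|
| Predictors and Covariate Analysis, first part | baseline variables | clinical improvement | predictor |
| Predictors and Covariate Analysis, second part | PSS and MEDI-Q over time | concurrent HDRS-17 change | association |
| Metabolomics | metabolite profiles and their changes | change in symptoms | association, then predictive biomarker |

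Only the third row lets a change over time carry the predictive label.

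**3. Overlap in time.** With samples and HDRS-17 both at T0, T1 and T2, the possible pairings are:

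- T0 metabolites with later HDRS-17 change: the explanatory variable comes first.
- T0-to-T1 metabolite change with T0-to-T1 HDRS-17 change: the same interval.
- T0-to-T2 with T0-to-T2: the same interval.
- T0-to-T1 metabolite change with T0-to-T2 HDRS-17 change: the first 12 of 26 weeks are shared, and the metabolite change is still unknown before treatment.

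The text allows all four. Only the first fits a predictor known before treatment.

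**4. Single-metabolite illustration.** Assume a metabolite whose baseline level is unrelated to the HDRS-17 change, and whose own change correlates r with it. The approximate power of a two-sided 5% test is Φ(atanh(r)·√(n − 3) − 1.96). For r = 0.3 and n = 96 this is Φ(0.3095 × 9.644 − 1.96) = Φ(1.025) ≈ 0.85. Simulation with 4,000 data sets per row gives:

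| n | r | change variable P<.05 | baseline level P<.05 |
|---|---|---|---|
| 96 | 0.3 | 85% | 5% |
| 96 | 0.5 | over 99% | 5% |
| 120 | 0.3 | 92% | 5% |
| 120 | 0.5 | over 99% | 6% |

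**5. PLS illustration.** Assumptions: n = 96; 10 metabolites with T0-T1 correlation 0.5; no baseline level predictive; 3 changes correlated r with the HDRS-17 change; one PLS component; 7-fold cross-validation; 400 data sets per scenario. The ranges cover repeated runs.

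| r | mean Q2, T0 only | mean Q2, T0 plus changes |
|---|---|---|
| 0 | -0.14 to -0.11 | -0.18 to -0.16 |
| 0.3 | -0.13 to -0.10 | 0.06 to 0.09 |
| 0.5 | -0.13 to -0.11 | 0.38 to 0.39 |

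The top-weighted variable, which is also the top VIP in a one-component model, is one of the three tracking changes in about 96% of data sets at r = 0.3 and in 100% at r = 0.5. Cross-validation returns a positive figure although nothing known before treatment predicts anything.

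**The case against.** The case for leaving the text alone is substantial, and much of it stands.

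- **No definition is breached.** A reader might infer that the Predictors and Covariate Analysis section defines a predictor as a baseline variable and that the Metabolomics section contradicts it. It does not define the term. It describes one baseline analysis and, separately, one concurrent analysis. It shows that the authors know the distinction, but it sets no rule for the metabolites.
- **No joint model is fixed.** A reader might also infer that profiles and changes enter one model together. The section speaks of analyses in the plural, and separate models are compatible with it. Which time points enter which model is the kind of detail an analysis plan may settle.
- **The aim is often worded as association.** The Introduction, the Study Design section and the Discussion all speak of relations or associations with treatment response. Against those aims, change-on-change models are on target.
- **The limits are disclosed.** The Analytical Methods section calls the biomarker work exploratory, hypothesis-generating and not powered for definitive associations. The Metabolomics section calls it secondary and proof-of-concept.
- **The illustration assumes its result.** Baseline value is set to zero and the tracking correlation is chosen. A reader might conclude that trackers will outrank baseline markers in this trial; that holds only under those assumptions. The usable n may also be below 96, because only specimens from cisgender women are analyzed and each sample type is optional.

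One thing is not answered. The sentence on predictive biomarkers follows directly from the models that include changes over time, and nothing restricts it to T0 metabolites. The exploratory label limits how certain a result is. It does not settle which time points may earn the word predictive.

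**Conclusion.** The point holds in a limited form. Followed as written, the Metabolomics section can label concurrent correlates of recovery as predictive, and its cross-validation step would not reveal this. The documents do not show that this will happen, only that nothing in the stated procedure prevents it.

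The size cannot be fixed from the documents, because it depends on how strongly metabolite changes track HDRS-17 change. Under the assumed correlations the apparent gain in Q2 from adding changes ranges from slightly negative (no tracking) to about 0.5 (r = 0.5: from about -0.12 to about 0.38).

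The primary HDRS-17 analysis, the randomization and the data collection are unaffected. The correction is worth making because it determines what the substudy can claim, but it concerns an exploratory component.

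**What to change.** In the Metabolomics section, or in the analysis plan that implements it:

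1. Base any claim of a predictive biomarker, the VIP selection behind it and the cross-validated performance on models with T0 metabolites only, with HDRS-17 change to T1 and to T2 as the outcomes.
2. Fit models of metabolite change against symptom change separately. Report them as concurrent associations, as is already done for PSS and MEDI-Q, without prediction metrics and without the word predictive.

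The cost is a few sentences and one extra model run. No new data are needed. The reported predictive performance will probably be lower. The Results section says that data analysis has not begun and that 8 participants were enrolled as of April 2026, so the change can still be made before any analysis.

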#### Missing Data

Following the ITT principle, LMMs will be applied without imputation, as they appropriately handle missing data under the missing at random assumption, and imputation may introduce unnecessary bias. Cluster and factor analyses will also be conducted without imputation, as they rely solely on baseline data, assuming that missingness is minimal and not systematic. Multiple imputation will be performed only for analyses that require it, such as multiple regression models and partial least squares regression.

All analyses will be 2-tailed, with statistical significance set at *P*<.05.

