### Biological Samples

#### Sample Types and Collection Procedures

Biological analysis will be conducted exclusively on specimens collected from cisgender women participants. Biological specimens to be collected include plasma, urine, saliva, fingernails, and hair. All collection procedures will adhere to standard operating procedures, with participant safety and comfort as priorities. Specific procedures for each biological sample are as follows:

Plasma: Blood samples will be collected using EDTA K2 plastic tubes (13 × 75 mm, 4 mL). Two tubes (totaling 8 mL) will be collected per participant on the day of the assessment visit.Urine: Participants will self-collect approximately 50 mL of midstream urine the night before their scheduled assessment visit, using a sterile 60-mL polypropylene container. The sample will be refrigerated overnight at the participant’s home and transported to the research facility on the day of the visit.Saliva: Participants will self-collect saliva samples the night before the assessment visit using 2 Salivette Cortisol collection devices. Samples will be refrigerated overnight at the participant’s home and transported to the research facility on the day of the visit.Fingernails: Participants will clip the distal ends of their fingernails at home before the assessment visit. Samples will be collected in sealed paper envelopes.Hair: A strand of hair (approximately 0.5 cm in diameter, or 50 mg for short hair) will be cut from the posterior vertex as close to the scalp as possible by trained personnel. The root end will be marked with a hair tie. Samples will be collected in sealed paper envelopes.

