### Data Analysis

#### Sample Size Calculation

A total sample size of 120 participants (60 per group) is required. This estimation was calculated based on a design with 2 groups and 3 measurement points. Assuming an effect size of *f* of 0.15, a significance level of *α* of .05, and a power of 0.90, with a correlation among repeated measures of 0.5 and assumed sphericity (*ε*=1), the minimum sample size estimated was at 96 patients. This number was increased to 120 to account for an anticipated 20% attrition rate. The sample size was determined using G*Power version 3.1.7.

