#### Statistical Analysis

The statistical analysis plan was developed in collaboration with 2 biostatisticians. The analysis will be performed using SPSS Statistics (version 26; IBM Corp.).

Descriptive statistics will summarize sociodemographic and biomedical variables at baseline. Metabolomic variables will be analyzed across all time points; a complete list of the metabolomic variables analyzed in each matrix is provided in Table S3 in Multimedia Appendix 1. Continuous variables will be presented as means and SDs or medians and IQRs, depending on the distribution, while categorical variables will be reported as frequencies and percentages.

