#### Informed Consent

All participants will receive detailed written and oral information about the study (ie, objectives, procedures, risks, and benefits) before enrollment. Once participants are informed, they will be asked to provide written informed consent for study inclusion. Specific consent will be obtained for the collection and future use of the biological samples; participants will be given the opportunity to decide which biological sample they wish to provide (ie, they may consent to provide some but not all biological samples).

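### Factor analysis is exempted from imputation as a baseline-only analysis, but the only factor analysis described is of metabolomic changes, which need follow-up samples

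*Protocol article*

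**What the plan says.** In the protocol article, the Missing Data section sets three rules. The mixed models are fitted without imputation. Multiple imputation is kept for analyses that need it, with multiple regression and partial least squares regression as the examples. For the remaining multivariate work the rule is "Cluster and factor analyses will also be conducted without imputation, as they rely solely on baseline data", and the sentence goes on: "assuming that missingness is minimal and not systematic".

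The Metabolomics section describes one factor analysis: "metabolomic changes will be assessed through exploratory factor analysis, grouping variables into latent factors". The Statistical Analysis section states: "Metabolomic variables will be analyzed across all time points". The Procedure section provides the later samples: "At T1 and T2, follow-up assessments will include the administration of primary and secondary outcome measures as well as biological sample collection".

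Three other places bear on how much will be missing:

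- Sample Size Calculation: "This number was increased to 120 to account for an anticipated 20% attrition rate".
- Informed Consent, on sample types: "they may consent to provide some but not all biological samples".
- Sample Types and Collection Procedures: "Biological analysis will be conducted exclusively on specimens collected from cisgender women participants".

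**The concern.** The exemption rests on two premises: that the analysis uses baseline data only, and that little is missing and not in a patterned way. The Metabolomics section contradicts the first for the one factor analysis it describes, because a change cannot be formed without a later sample. The second is hard to hold for change data when the protocol itself expects one woman in five to be lost and lets each woman choose which samples to give.

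At stake is the coherence of the missing-data rule for part of the exploratory metabolomics component. As written, an analyst who follows the rule has no valid reason for leaving the change data unimputed in the factor analysis while imputing the same kind of data in the regressions. Women with follow-up samples may differ from those without, so factors of change could describe a selected subset, and nothing in the plan would make the reader aware of it.

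**Working it through.** **1. The plan's own figure.** Inputs from Sample Size Calculation: f = 0.15, α = 0.05, power 0.90, 2 groups, m = 3 measurements, correlation ρ = 0.5, ε = 1. For the group-by-time interaction in a repeated-measures ANOVA:

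- λ = f² × N × m / (1 − ρ) = 0.0225 × 96 × 3 / 0.5 = 12.96
- df1 = (2 − 1)(3 − 1) = 2; df2 = (96 − 2)(3 − 1) = 188
- Power from the noncentral F is 0.902 at N = 96 and 0.896 at N = 94, so 96 is the minimum with equal groups.
- Inflation for attrition: 96 / (1 − 0.20) = 120.

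The stated 96 and 120 both reproduce. No number in the plan is disputed here.

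**2. The sections side by side.**

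| Question | Missing Data | Elsewhere in the article |
|---|---|---|
| Which visits does the factor analysis use? | Baseline only | Changes (Metabolomics); all time points for metabolomic variables (Statistical Analysis); samples at T1 and T2 (Procedure) |
| How much is missing? | Minimal | 20% attrition expected (Sample Size Calculation); each sample type optional (Informed Consent) |
| How are metabolite changes handled when missing? | Not imputed in factor analysis; multiply imputed in multiple regression and partial least squares | The regressions are also fitted to metabolite changes over time (Metabolomics) |

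The first row is a direct conflict. The second undercuts the remaining premise once change data are involved. The third shows that the difference in treatment depends on the baseline-only reason.

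**3. Size on the protocol's own assumption.** Women without complete change data: 120 × 0.20 = 24. Women left: 120 × 0.80 = 96. This takes attrition to mean that the last sample is missing. The article does not say when the losses fall, so for change to 12 weeks alone the number could lie between 96 and 120.

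**4. Further loss, not quantified in the documents.** The article gives neither a consent rate per sample type nor the number of transgender participants. As an illustration for a single matrix, with an assumed consent rate c unrelated to attrition, the number left is 96 × c:

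- c = 0.95: 91.2, about 91
- c = 0.90: 86.4, about 86
- c = 0.80: 76.8, about 77

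Only the 96 rests on a figure in the document. The other three rest on assumed rates.

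**The case against.** The strongest reply is that the Metabolomics sentence may be the loose one. If factors are defined at baseline and later visits are scored on the same loadings, the factor extraction really does use baseline data only. The article does not say this, and assessing change would still need the T1 and T2 values, so the conflict remains. The reply does show that the request should be to reconcile the two sections, without presuming which one is wrong.

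A second reply is that this work is declared exploratory, unpowered and secondary. That is true, and it limits the weight of the point.

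Three stronger readings are tempting, and the documents do not support them:

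- A reader might infer that the factor analysis is restricted to women who gave every sample type at every visit. The plan says only that nothing is imputed. It does not specify listwise deletion, and it does not put the five matrices into one factor analysis. Severe losses from such a pooled complete-case analysis cannot be attributed to the plan.
- A reader might infer that conclusions about metabolic change and treatment response rest on this selected group. The Metabolomics section gives that task to partial least squares and multiple regression, which are imputed. It nowhere says that factor scores enter those models.
- A reader might object that a cluster analysis is named under Missing Data and described nowhere else. A condensed article may leave that to the full plan, and whether it uses baseline data only can be neither confirmed nor refuted here.

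**Conclusion.** The contradiction stands. The justification for leaving factor analysis without imputation does not apply to the factor analysis that the article describes. This is a stated rule with a stated reason that another section contradicts, so an unseen analysis plan does not excuse it.

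On the expected attrition, about 24 of 120 women lack complete change data and about 96 remain, before declined sample types and the cisgender-only restriction. This assumes full recruitment and that attrition means missing follow-up samples. A fifth of the sample is not minimal.

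The consequence is confined to the exploratory factor-analysis step. The HDRS-17 mixed model, the secondary outcomes, the sample size and the imputed response models are unaffected. It is worth correcting, but it does not threaten the trial's main conclusion.

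**What to change.** Reconcile the Metabolomics and Missing Data sections in one of two ways:

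1. State under Metabolomics that factors are derived from baseline metabolites only and that T1 and T2 values are scored on those loadings. State also that missing follow-up is handled as in the other longitudinal analyses. The baseline-only sentence then holds for the extraction of factors.
2. Keep the factor analysis of changes. Limit the no-imputation sentence to analyses that truly use baseline data only, and name an all-available-data method for the changes: a covariance matrix estimated by the EM algorithm, or the multiple imputation already planned for the regressions.

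Under either option, report the number of women analysed per matrix, and replace the assumption of minimal missingness with one that fits the expected attrition and the optional consent.

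The cost is a few sentences and a routine estimation choice, with no change to data collection or sample size. The Results section reports 8 women enrolled as of April 2026 and no analysis begun, so the choice can still be made before any data are analysed.
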